# Morbidity surveillance

Throughout the first year of life reporters will complete morbidity reports, which will be reviewed weekly by medical staff and then fortnightly to age 18 months. Parents will be encouraged and assisted to bring children in to the PNGIMR for examination and treatment if sick. Blood culture and nasal swab will be done on children with cough and raised respiratory rate (77). Children with moderate pneumonia (lower chest wall indrawing) or severe pneumonia (chest indrawing and enlarged liver or cyanosis) will be hospitalised; blood culture, nasal swab and a chest x-ray will be taken. CXRs will be read by the senior physician ([name]) and a sample then reviewed by a radiologist recommended by the WHO radiology group.

**iii) Safety monitoring board**

A safety monitoring board (SMB) will be established, including independent clinicians from PNG and Australia. If the board finds nothing untoward following the first block of 52 immunizations of groups 2 and 3, the trial will then be authorized to proceed including neonatal immunization (group 1). Clinical and immunogenicity data will be sent regularly to the clinical monitors. Throughout the study, all adverse events will be reported and any serious adverse events will be immediately reported to the SMB. In particular, they will examine the data for any evidence of tolerance/immune suppression in addition to serious adverse events.

# **iv) Specimen collection**

This study will involve collection of cord blood and a total of 6 blood samples over the first 18 months of life (3 samples before 6 months). Nurses at PNGIMR have extensive experience in venepuncture for culture and immunogenicity studies in young infants (5, 76). Preparation of PBMCs also allows for collection of 1.5-2ml plasma, which will be defibrinated and used for serological assays (IgG subclasses, OMP IgG) if insufficient serum is collected. This has been validated in our laboratory and defibrinated plasma is the source for the WHO pneumococcal QC sera. All specimens will reach the laboratory within 2 hours.

*Serum* (2-4ml) will be taken at birth (cord), 2, 3 and 4 months of age (initial responses to 1, 2 and 3 doses of PCV), 9 and 10 months (pre- and post-PPV booster) for memory to PCV serotypes, and for antibody persistence at 18 months.  Pnc serotype-specific IgG antibodies in serum will be measured on all samples. CPS IgG and IgG subclasses will also be measured. *Heparinised blood* (3-5ml) will be collected for T-cell cytokine studies from cord blood and at 3, 9, 10 and 18 months of age to examine development of Pnc and vaccine-specific immunity as well as overall development of Th1/Th2 immunity. This amount of blood has proven sufficient in previous studies by our group (65) for the assays proposed.

**Table 2. Outline of Serological and Cellular Assays Performed at Each Timepoint**

| Sample | Antigens | Birth* | 1  month | 2  months | 3  months | ~~4~~  months | 9  months | 10  months | 18  months |
| --- | --- | --- | --- | --- | --- | --- | --- | --- | --- |
| Serum  (2-4ml) /  Plasma | CPS IgG* | X |  | X | X | X | X | X | X |
| CPS IgG Avidity† | X |  | X |  | X | X | X |  |
| CPS IgG1 & IgG2† | X |  |  | X |  |  | X |  |
| Pnc OMP IgG‡ | X |  |  | X |  | X |  | X |
| PBMC  (3-5ml) | PHA, LPS/IFN, PPD, SEB | X |  |  | X |  | X | X | X |
| CRM197, DT, TT, OMP‡, HDM, RSV |  |  |  | X |  | X | X | X |
| Measles |  |  |  |  |  | X | X |  |
| Saliva  (1-2 ml) | CPS IgA† |  |  | X |  | X |  | X | X |
| Pnc OMP‡ |  | X |  | X |  | X | X | X |

* Pnc CPS types 4, 5, 6B, 9V, 7F, 14, 18C, 19F, 23F; † Pnc CPS types 6B, 7F, 14, 19F; ‡ pneumococcal OMPs PspA, PsaA, Ply

*Saliva*samples will be examined for mucosal IgA responses to vaccine and Pnc antigens. Saliva (1-2ml) will be collected using surgical eye spears, transported to the laboratory at 2-8C, centrifuged and stored at –70C. PNGIMR staff have experience in saliva collection. We have evaluated different saliva collection methods and found salivary Pnc CPS IgA collected by eye spears similar to collection by direct suction ([name] unpublished). Eye spears are being used in a infant cohort study in Kalgoorlie, WA, and Pnc IgA assays have been successfully completed on these samples ([name], pers comm).

####

#### *Pernasal swabs* will be collected to determine the effect of early carriage on subsequent responses to PCV and the development of Pnc immunity and also the impact of neonatal PCV on URT carriage. Swab collection, transport and storage will employ a standardised methodology (78) which has proven to be very effective in our earlier studies in PNG (16) and Australia (11,18).

#### v) Laboratory methods

All laboratory staff will be blinded to subject treatment group.

*Bacteriology*:Standard procedures established at PNGIMR for bacterial isolation from pernasal swabs will be used, including the use of selective media and semi-quantitative assessment of colonisation density (15, 16). Samples will be stored for characterisation of respiratory pathogens other than Pnc. Serogrouping will be done on 4 Pnc colonies per plate by the Quellung reaction to detect multiple populations. Serotyping (e.g. type 6A or 6B) will be performed where appropriate by the Pneumococcal Reference Laboratory, Brisbane, through an existing relationship with PNGIMR. To examine effects of PCV on the prevalence of antibiotic-resistant isolates, antimicrobial susceptibility of Pnc will be determined by disk diffusion and suspected resistance confirmed by E-test.

*Pnc serology:* Serological testing of serum and saliva will be performed at PNGIMR under the supervision of [name]. Serotype-specific Pnc IgG serum antibodies will be measured by the standardised WHO enzyme-linked immunosorbent assay (ELISA) as previously described (21, 24) modified with preincubation of unknown sera with cell-wall polysaccharide and CPS 22F to improve assay specificity as recommended. The sera will be assayed for IgG for all seven PCV serotypes as well as non-PCV serotypes 5 and 7F that are important causes of IPD in PNG. International quality control sera (provided by [name], WHO Pneumococcal Serology Reference Laboratory, London) will be used to ensure consistent assay performance.

The amount of serum (or plasma) and saliva available may limit the number of additional serological investigations that can be performed. A summary of assays proposed at each time point is shown in Table 2. At least 4 representative serotypes will be selected for each assay to allow correlation between assays for serotype- specific results. These include PCV serotypes 6B, 14 and 19F (all common carriage isolates and causes of IPD in PNG) and non-PCV serotype 7F, which is the most common cause of IPD in young PNG infants (79). Antibody avidity for CPS IgG antibodies will be assessed in PNG using a modified elution ELISA with the chaotrope, sodium thiocyanate (NaSCN) as described (80) with modifications for the WHO Pnc ELISA. Avidity index is the concentration of NaSCN resulting in a 50% reduction in OD. Serotype-specific Pnc IgG1 and IgG2 subclass antibodies will be assayed in sera (or defibrinated plasma) at selected time points by standardised ELISA with 89SF reference sera as above with substitution of appropriate monoclonal enzyme conjugate. Serum IgG responses to Pnc OMPs PspA, PsaA and Ply will also be measured by ELISA as described (57).

Salivary ELISA methods that have been established (through collaboration with [name]’s laboratory) to measure IgA responses to selected CPS serotypes (6B, 7F, 14, 19F) (44), and Pnc OMPs, PspA, Ply and PsaA (58), on samples as shown in Table 2. Pnc salivary IgA will be expressed as percentage of total salivary IgA. The low CPS antibody concentrations in saliva and limitations on the amount able to be collected will mean that only CPS or Pnc OMPs will be measured at time points <10 months of age (Table 2).

##

## Concomitant vaccine responses: Antibody responses to diphtheria toxoid (DT), tetanus toxoid (TT) and Hib at 4 months of age will be measured by standardised ELISA as previously described (81). Hepatitis B antibody will be measured using a routine clinical laboratory assay. Children having antibody levels that are not protective will be offered the appropriate booster immunization(s).

*Cellular immune responses:* Adaptive and innate immune functions will be assessed in children at birth, and at 3, 9, 10 and 18 months of age, employing methods in current usage in prospective cohort studies in Perth. The [name] laboratory has developed robust methods for immunoepidemiological field studies based upon on‑site collection of blood, and local processing to yield purified peripheral blood mononuclear cells (PBMC) which are immediately cryopreserved, and subsequently shipped under liquid nitrogen to a central laboratory for later assay. The T‑cell culture systems comprise bulk culture stimulation employing 0.5x106 cells per sample, to minimise detection problems associated with low frequency of circulating responder cells.

The choice of sampling times for T-cell studies (cord, 3, 9,10 and 18 months) is based on results from our earlier studies (64, 65) and from ongoing cohort studies. Our interest in cord blood analysis is based on recent results suggesting that neonatal cytokine production profiles are predictive of immune response capacity at age 2‑4 years (82). The sample at 3 months was chosen to provide a profile of early T‑cell immunity to Pnc antigens in unvaccinated subjects, versus those who had been given 3 vaccine doses commencing at birth or delayed until one month of age. Secondarily, it will permit assessment of possible effects of PCV on postnatal maturation of overall immune competence and/or responsiveness to index vaccine components (DT, TT). The bleeds at 9 and 10 months will permit us to assess firstly the stability of PCV carrier-specific T‑cell immunity in the different groups (6 months after the last vaccine dose), and secondly will permit assessment of the effects of PCV on the memory T‑cell response to measles, which is the third index vaccine in the study. The final bleed at 18 months will provide data on T‑cell memory to the PCV vaccine, and a logical end-point to the section of the study involving assessment of kinetics of postnatal maturation of immune functions.

An additional important aspect of the study involves assessment of T‑cell immunity to Pnc antigens, and to this end we have obtained supplies of Pnc OMPs PspA, Ply and PsaA from [name], Adelaide. During the early phase of the study we will assess antibody responses to the individual Pnc OMPs, and from these results select a single Pnc OMP for the main T‑cell studies. Initial pilot experiments in our laboratories suggest PspA is the likeliest candidate. Responses to the PCV carrier protein (CRM197) will also be measured.

Analysis of T‑cell responses to concomitant vaccines will focus on TT and DT, and measles extract, as in current usage in T‑cell studies in our labs. This will provide information relevant to immunological safety of neonatal PCV, notably whether it modulates responses to these other vaccines e.g. via enhancement of normal postnatal maturation of Th1/Th2 functions. The latter will be independently measured via responsiveness to the polyclonal T‑cell mitogen PHA, and the innate immune system stimuli LPS/IFN, as in earlier studies (64, 65). An additional aspect of immunological safety monitoring will focus on potential bystander effects of reduction in carriage by PCV on respiratory mucosal homeostasis. Effects on susceptibility to viral infections such as respiratory syncytial virus (RSV), or responses to inhalant allergens, in particular house dust mite (HDM), may result in increasing respiratory tract symptoms such as wheeze and accordingly we will include RSV and HDM in the test panel. If enough cells are available, PPD (purified protein derivative of *M. tuberculosis*)and SEB (staphylococcal enterotoxin B) will be included as these provide valuable additional information on responsiveness of infants to microbial stimuli (82).

Cytokine analyses will be carried out by quantitative real-time PCR (Taqman) on cell culture pellets, or on culture supernatants by ELISA (techniques in routine use in Perth). Cytokines to be measured by ELISA will be IL‑5, IL‑6, IL‑10, IFN, IL‑12 and TNF. We have determined that these cytokines are readily detectable at the protein level in the majority of infants 3 months of age. Cytokines to be measured by PCR (due to low production levels and/or unavailability of ELISA reagents) will be IL‑4, IL‑9, IL‑18 and IL‑23. The choice of cytokines to be measured is based upon our earlier experience with cohort studies in Perth infants. The Th2 cytokines IL‑4, IL‑5, IL‑9 and IL‑13 dominate vaccine responses in early infancy in Australian subjects, with the pattern changing towards a mixed and/or Th1‑dominated (IFN) response by 18 months. If “neonatal tolerance” phenomena are operative in some Pnc responses, these may be revealed as Th2‑polarised memory and hence it will be important to obtain comprehensive information on these latter cytokines. Alternatively, Th1 immunity may develop in PNG infants much more rapidly postnatally as a result of more vigorous microbial stimulation of the immune system and if so this has important implications for vaccine efficacy and safety. Accordingly we will expand the range of Th1-associated cytokines to be measured to IFN, TNF, IL‑18 and IL‑23, and include IL‑12 which plays a dominant role in driving the Th1 pathway. IL‑6 and IL‑10 are important regulatory cytokines produced by both T‑cells and monocytes/macrophages, IL‑10 being of particular interest because of its potential connection with T‑regulator cell activity.

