### Table 1. Neonatal Immunization with Pnc Conjugate Vaccine Study Outline

|  | Birth | 1 -3wk | 1mth | 2mths | 3mths | 4mths | 6 mths | 9mths | 10mths | 18mths |
| --- | --- | --- | --- | --- | --- | --- | --- | --- | --- | --- |
| Group 1 Neonatal PCV | HepB, BCG, OPV, PCV |  | DTP/Hib, HepB, OPV, PCV | DTP/ Hib, OPV, PCV | DTP/ Hib, OPV, HepB |  | Measles | PPV Measles |  |  |
| Group 2 Infant PCV | HepB, BCG  OPV |  | DTP/Hib, HepB, OPV, PCV | DTP/Hib, OPV, PCV | DTP/Hib, OPV, HepB, PCV, |  | Measles | PPV Measles |  |  |
| Group 3 Control | HepB, BCG  OPV |  | DTP/Hib, OPV, HepB | DTP/Hib, OPV | DTP/Hib, OPV, HepB |  | Measles | PPV Measles |  |  |
| Nose Swab |  | weekly | X |  | X |  |  | X |  | X |
| Saliva 1-2 ml |  |  | X | X | X | X |  | X | X | X |
| Serum 2-4 ml | **X*** |  |  | X | **X** | **X** |  | **X** | **X** | **X** |
| PBMC 3-5ml | **X*** |  |  |  | **X** |  |  | **X** | **X** | **X** |
| Morbidity surveillance |  |  |  |  |  |  |  |  |  |  |

HepB: hepatitis B vaccine; PCV: 7-valent Pnc-CRM197 conjugate vaccine; OPV: oral polio vaccine; DTP: diphtheria-tetanus-whole-cell pertussis; Hib: *Haemophilus influenzae* type b tetanus toxoid conjugate vaccine (PRP-T); PPV: 23-valent Pnc polysaccharide vaccine

***** Cord blood sample: total 10ml taken for PBMC (peripheral blood mononuclear cells)

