# Immunization schedule and follow-up

Village reporters will inform study staff if a woman has delivered outside hospital. A study nurse will visit the delivery ward at Goroka Hospital at least once daily to identify newborns to enrolled women. Following recruitment, infants will be randomized to one of three equal-sized groups to receive: 1) PCV at ages 0-1-2 months, 2) PCV at ages 1-2-3 months and 3) no PCV. Birthweight and weight at each follow-up visit will be recorded. Routine infant immunizations will be given in accordance with the PNG schedule (Table 1). As PCV has not been evaluated in this population previously, the first 52 infants will be randomized to groups 2 or 3 only, and the safety data will be reviewed by an independent safety monitoring committee. Conjugate Hib vaccine (ActHib), which is mixed with DPT, has recently been introduced into the immunization schedule in PNG, after being shown to be safe and immunogenic in this population when given at ages 1, 2 and 3 months (76). Since it is in short supply, we may have to purchase it. BCG and DPT/Hib are routinely administered in the deltoid muscle. Hepatitis B and measles will be given in the right thigh. PPV (at 9 months) and PCV will be given in the left thigh.

All immunizations will be given either in Goroka Hospital or at the PNGIMR clinic. Following immunization, children will be monitored at the clinic for 2 hours. Children will then be seen 1 and 2 days after each dose during primary immunization and on day 7 following PPV to check for local or systemic reactions. Children will be seen weekly by nursing staff to age 4 weeks. Guardians will be informed of time of appointments and transport to Goroka clinic will be arranged. If they fail to attend their appointment, we will make 3 further attempts to bring the children for routine follow-up. Guardians may choose to remove their child from the study at any time. Participants will cease to be in the study if they suffer an allergic reaction to vaccination or have inadvertently been given routine immunizations by someone other than the study nurses. All such children will continue to receive medical attention from clinic and field staff as required.

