PNG infants remain at ongoing risk of IPD in the first 5 years of life. Long-term protection induced by PCV depends on the successful priming for immunologic memory so infants can mount brisk anamnestic antibody responses on subsequent challenge. All infants will receive 23-valent PPV at 9 months of age (6 months after their primary course) to evaluate the induction of memory to PCV serotypes. These serotypes in PPV are not immunogenic in PNG infants at age 9 months (except for 23F) (24) so that significant IgG responses to PCV serotypes compared to PCV-naive controls will indicate the induction of memory. This vaccine is efficacious from age 6 months and provides some cover against serotypes which are important causes of IPD in this population. Antibody avidity maturation (post-primary to post-booster immunization) will also be assessed as it is a surrogate marker for the induction of memory after conjugate vaccines (39, 80, 81) and influences the functional capacity of antibodies produced (35). Avidity maturation will be assessed by comparing changes in avidity index between 4-, 9- and 10-month samples in comparison to controls. Antibody persistence will be evaluated with blood samples at 18 months of age.

*4. The impact of neonatal versus early infant vaccination upon nasal carriage of pneumococci*

Reduction in the burden of early Pnc carriage in the critical neonatal period may have an important impact on early disease as well as the development of long-term immunity to Pnc infections. Regular carriage sampling in the first month of life will assess the impact of neonatal PCV immunization, and carriage will be assessed at regular intervals thereafter to determine persisting effects of PCV on carriage compared to controls.

*5. The impact of early colonisation with vaccine serotypes on antibody responses (systemic and mucosal) to neonatal and early infant immunization with PCV*

In the Asaro Valley 60% of infants acquired Pnc in the URT by 15 days of age. PCV serotypes are responsible for 59% of carriage isolates in the first 3 months of life in PNG (16). Swabs will be collected at weekly intervals during the first month to identify children with early ( 2 weeks) colonisation. This will allow evaluation of the effects of early colonisation on systemic antibody responses to subsequent PCV immunization. Effects of time of colonisation and PCV on mucosal immunity (salivary IgA responses to Pnc CPS and OMPs) will also be assessed .

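### The protocol describes both PCV groups as having had 3 doses at the 3-month T-cell sample; by its own schedule group 2 has had 2, so a group 1 versus group 2 T-cell difference at that age cannot separate neonatal priming from an extra carrier dose

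*Protocol*

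**What the plan says.** Immunization schedule and follow-up defines the groups as "1) PCV at ages 0-1-2 months, 2) PCV at ages 1-2-3 months and 3) no PCV", and Overall study design says the same. In Table 1 the group 2 entry at 3 months reads "DTP/Hib, OPV, HepB, PCV", so the third group 2 dose falls at the visit at which the PBMC sample is also taken.

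Specimen collection says that heparinised blood "will be collected for T-cell cytokine studies from cord blood and at 3, 9, 10 and 18 months of age". Tables 1 and 2 agree: there is no PBMC sample at 4 months.

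Laboratory methods, explaining the choice of T-cell sampling times, describes the 3-month sample as a comparison of unvaccinated infants "versus those who had been given 3 vaccine doses commencing at birth or delayed until one month of age". It describes the later bleeds as "6 months after the last vaccine dose", without distinguishing the groups.

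Two other places use one dose count or interval for everyone. Specimen collection says that serum "will be taken at birth (cord), 2, 3 and 4 months of age (initial responses to 1, 2 and 3 doses of PCV". Specific scientific questions, question 3, says "All infants will receive 23-valent PPV at 9 months of age (6 months after their primary course".

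**The concern.** The 3-month sample is the only early T-cell sample after vaccination, and the protocol credits it with equal dose number in the two vaccine groups. The schedule does not give it that property.

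This bears on interpretation. Question 8(a) measures T-cell cytokine responses in all three groups to learn whether neonatal PCV shifts the Th1/Th2 balance. It names the CRM197 carrier and the closely similar diphtheria toxoid as the route by which this might happen. The Background section on conjugate vaccines notes that, for some combination vaccines, more carrier protein can impair antibody responses. Dose number is therefore a plausible cause of a group difference in its own right. Someone relying on the Laboratory methods text would think it had been held equal.

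**Working it through.** **Inputs.** PCV ages are 0, 1, 2 months (group 1) and 1, 2, 3 months (group 2), from Immunization schedule and follow-up and Table 1. Postnatal serum is taken at 2, 3, 4, 9, 10 and 18 months and PBMC at 3, 9, 10 and 18 months, from Specimen collection and Table 1. DTP/Hib is given at 1, 2 and 3 months in every group, from Table 1.

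**Rule.** At sampling age t, prior doses = number of PCV ages below t, and interval = t minus the latest PCV age below t.

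**The plan's own figure, 3 doses in each PCV group at 3 months.** Group 1: ages 0, 1, 2 are below 3, giving 3 doses, so the figure is reproduced. Group 2: ages 1 and 2 are below 3, giving 2 doses, so it is not. Group 2 reaches 3 only if the dose due at that visit is counted. A dose given that day could not yet have produced a response, and Specimen collection assigns the same sample to 2 doses: "2, 3 and 4 months of age (initial responses to 1, 2 and 3 doses of PCV".

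**All sampling ages:**

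| Age (months) | Group 1: doses (months since last) | Group 2: doses (months since last) | PBMC taken? |
|---|---|---|---|
| 2 | 2 (2 − 1 = 1) | 1 (2 − 1 = 1) | no |
| 3 | 3 (3 − 2 = 1) | 2 (3 − 2 = 1) | yes |
| 4 | 3 (4 − 2 = 2) | 3 (4 − 3 = 1) | no |
| 9 | 3 (9 − 2 = 7) | 3 (9 − 3 = 6) | yes |
| 10 | 3 (10 − 2 = 8) | 3 (10 − 3 = 7) | yes |
| 18 | 3 (18 − 2 = 16) | 3 (18 − 3 = 15) | yes |

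**What follows.**

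1. At 3 months the groups differ in dose number only. Both are one month after the last prior dose.
2. CRM197 exposures before the 3-month bleed are 3, 2 and 0 in groups 1, 2 and 3. Prior DTP/Hib doses are 2 in all three.
3. The earliest PBMC sample with a complete series in both groups is at 9 months, with a one-month difference in interval.
4. The mapping of 2, 3 and 4 months to 1, 2 and 3 doses fits group 2. For group 1 those samples follow 2, 3 and 3 doses.
5. The 6-month interval to the 9-month visit fits group 2 (9 − 3 = 6). For group 1 it is 9 − 2 = 7.

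**The case against.** The case for leaving most of this alone is substantial. Doses received by a given age are part of what distinguishes a 0-1-2 from a 1-2-3 month schedule, so comparing schedules at the same age is legitimate. Question 2 says openly that the 2-month antibody comparison sets the second neonatal dose against the first dose at 1 month. Its stated primary contrast is neonatal PCV against control. Laboratory methods also frames the 3-month sample mainly as unvaccinated against vaccinated infants and nowhere says that a group 1 versus group 2 difference will be ascribed to neonatal priming. All of that stands, but it does not make the dose statement for group 2 true. Question 8(a) measures all three groups, so the comparison is available to be made.

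The order of bleed and injection within a visit is not stated outright. The dose mapping in Specimen collection implies bleed first, and the conclusion does not depend on it, because a same-day dose could not yet show.

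Two stronger readings are tempting. A reader might infer that the antibody contrasts are biased too, because group 1 has had an extra month of decay at 4 months. The protocol gives no decay rate, and its Background suggests natural boosting by carriage after priming, so neither size nor direction can be derived. A reader might also infer a bias in the 4-month safety assessment. The antibody endpoints named there for concomitant vaccines are diphtheria, tetanus and Hib, and DTP/Hib timing is identical in all groups. At most the diphtheria response could be touched indirectly, through its similarity to CRM197. Neither reading is supported as a bias.

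**Conclusion.** The contradiction is real and limited. Laboratory methods attributes 3 doses to both PCV groups at the 3-month T-cell sample; the schedule gives 3 and 2. The discrepancy is one dose, in one of two vaccine groups, at the only early post-vaccination PBMC sample. With no 4-month PBMC sample it cannot be removed in analysis, so the 3-month group 1 versus group 2 T-cell contrast compares 3 with 2 doses as well as birth with one-month start.

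Contrasts of either PCV group with control remain interpretable, provided the group 2 contrast at 3 months is read as following 2 doses. The primary outcome and the sample size are unaffected. The unqualified dose mapping for serum and the single 6-month interval are smaller slips of the same kind, the latter by one month for group 1.

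This rests on visits occurring at the nominal ages and on the schedule in Table 1 being the one in force. It should be corrected because it changes what the 3-month T-cell comparison can conclude.

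**What to change.** Reconcile the sampling-time text in Laboratory methods with Table 1. If the Table 1 schedule stands, state that:

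- the 3-month T-cell contrast of groups 1 and 2 is 3 versus 2 prior doses;
- the interpretable 3-month contrasts are each PCV group against control, with group 2 after 2 doses;
- the first complete-series T-cell contrast of groups 1 and 2 is at 9 months, 7 versus 6 months after the last dose.

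In Specimen collection, limit the mapping to 1, 2 and 3 doses to group 2. In Laboratory methods and question 3, replace the single 6-month interval with one per PCV group.

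Optionally, add a supplementary antibody contrast from sera already planned: group 1 at 3 months against group 2 at 4 months, both one month after dose 3. It must be disclosed that the two sides differ by one month of age and by 2 versus 3 prior DTP/Hib doses. The second difference matters because diphtheria toxoid resembles the carrier. This contrast can only sit beside the same-age comparisons.

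The cost is a few sentences and, if the option is taken, one extra table. No dose, visit or sample changes.
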